## Abstract

**Background:**

Palliative radiotherapy (PRT) is an effective treatment for managing symptoms of advanced cancer. At least half of all radiation treatments are delivered with palliative intent, aimed at relieving symptoms, such as pain or shortness of breath. Symptomatic patients must receive PRT quickly, therefore expeditious treatment planning is essential. Standard radiation planning requires a dedicated CT scan acquired at the cancer centre, called a ‘CT simulation’, which facilitates treatment planning (i.e. tumor delineation, placement of radiation beams and dose calculation). However, the CT simulation process creates a bottleneck and often leads to delays in starting treatment. Other researchers have indicated that CT simulation can be replaced by the use of standard diagnostic CT scans for target delineation and planning, which are normally acquired through the radiology department as part of standard patient workup.

The goals of this feasibility study are to assess the efficacy, acceptability and scalability of diagnostic-CT-enabled planning, compared to conventional CT simulation planning, for patients receiving PRT to bone, soft tissue and lung disease.

**Methods:**

This is a randomized, phase II study, with 33 PRT patients to be randomized in a 1:2 ratio between conventional CT simulation (Arm 1), and the diagnostic CT enabled planning workflow (Arm 2). Patients will be stratified by treatment target volume (bone and soft tissue metastasis vs. primary or metastatic intrathoracic disease targets).

The primary endpoint is the amount of time the patient spends at the cancer centre. Secondary endpoints include efficacy (rate of plan deliverability and rate of plan acceptability on blinded dose distribution review), stakeholder acceptability (based on patient and clinician perception of acceptability questionnaires) and scalability.

**Discussion:**

This study will investigate the efficacy, acceptability and scalability of a “sim-free” PRT pathway compared to conventional CT simulation. The workflow may provide opportunity for resource optimization by using pre-existing diagnostic imaging and requires minimal investment due to its similarity to current PRT models. It also offers potential benefit to patients by eliminating an imaging procedure, reducing the amount of time spent at the cancer centre, and expediting time to treatment.

**Trial registration:**

Clinicaltrials.gov identifier: NCT05233904. Date of registration: February 10, 2022; current version: 1.4 on April 29, 2022.

**Supplementary Information:**

The online version contains supplementary material available at 10.1186/s12904-022-01115-y.

## Background

Palliative radiotherapy (PRT) is an effective and efficient intervention in managing the symptoms of advanced cancer [1]. At least half of all radiation treatments are delivered with palliative intent [2], and symptom relief is reportedly experienced by 60-80% of recipients [3]. Treatment indications are broad, but localized pain from bone (and soft tissue) metastases and thoracic PRT for dyspnea and airway preservation are the most frequent indications and are estimated to account for 35-40 and 25% of all courses respectively [4, 5].

The PRT workflow typically involves a radiation oncology (RO) consultation, CT simulation appointment, treatment planning, quality assurance (QA), and treatment delivery. 3D CT-simulation for target delineation and dosimetry is considered the gold standard [6] in most radiotherapy departments and represents a major checkpoint in the patient care pathway.

Expediency is also a key component of PRT [7]. The implementation of rapid access PRT programs has streamlined the referral-to-treatment pathway, reduced wait times, decreased the number of required hospital visits, and resulted in improved patient satisfaction [8–11]. However, these newer models of care still depend upon a conventional workflow, a process that usually takes at least 4 hours and translates into significant wait times, in some cases even dissuading patients from receiving same-day service. This model also requires reserved or readily available CT-simulation appointments, which can be a scheduling challenge. In a local context, strategic resource planning for decommissioning and replacement of two CT-simulators has underscored the need to explore resource optimization.

Such efforts are not only relevant to short-term pressures resulting from machine replacement, but also because demands on the cancer care system and radiation programs are only anticipated to increase. Cancer is the leading cause of death in the province, nearly one out of every two Ontarians will develop cancer in their lifetime, and incidence is only expected to rise as the population ages [12]. Additionally, as treatments improve, many patients live longer and require more PRT courses than patients in the past (the number of people treated with radiation has grown by about 2% per year since 2012). Sustainability will not only depend on managing existing resources, but on optimizing them through innovative models of care.

Several authors [10, 13–19] have explored alternatives to the conventional PRT pathway, and specifically opportunities to obviate the need for CT-simulation. Wong R and colleagues [13] demonstrated the dosimetric validity and clinical feasibility of using cone beam CT (CBCT) acquired on the treatment unit to plan PRT treatments. This workflow successfully eliminates CT-simulation but still entails significant “on-bed” times for patients (ranging from 30 to 50 minutes), requires seamless and synchronous multidisciplinary team (MDT) collaboration, and “pressurizes” the QA process. Patient satisfaction in the CBCT pathway was reported as “equivalent,” but there was no control group and no citation of conventional PRT satisfaction. The most common patient complaint was having to remain motionless on the treatment bed for the duration of the appointment (mean ± SD time of 32.7 ± 4 minutes). The workflow has since been discontinued due to challenges with scheduling and RO availability.

Wong S and colleagues [10] propose an alternative workflow, which utilizes recent diagnostic CT (dCT) scans. In this sequential 2-phase investigation, the authors confirmed dosimetric validity and demonstrated efficacy in a prospective cohort of 30 PRT patients. Participants still underwent CT-simulation/planning to ensure a “back-up” plan was available, but the authors reported 100% deliverability with dCT plans and dosimetric variation consistent with similar investigations [13, 14].

Using the workflow described above, Schuler and colleagues [20] subsequently investigated pain response for 160 PRT patients using electronic patient-reported outcomes. Given that only the planning image dataset had changed (from CT simulation to diagnostic-CT), they hypothesized and confirmed that overall and complete pain response rates were equivalent to published evidence [21].

This proposed feasibility study will evaluate a diagnostic-CT-enabled planning workflow and assess efficacy, acceptability and scalability. The workflow will employ CBCT-planning as a back-up pathway and incorporate optical surface guidance for ease of set-up reproducibility. The study will also expand eligibility criteria from previous work to include thoracic disease targets in addition to bone and soft tissue disease. Pain response or treatment response were not chosen as endpoints given previous evidence of equivalency and/or the reasonable assumption of equivalency as both arms of the investigation ultimately receive the same treatment. The only difference between arms is the planning image set. Thus, the evaluation of the efficacy of the diagnostic-CT-enabled planning workflow, in this context, is dependent upon the rate of plan deliverability (i.e. the experimental planning arm produced a deliverable plan) and acceptability (i.e. the experimental planning arm produced a plan determined to be acceptable as per institutional guidelines).

## Objectives

To assess the efficacy, acceptability and scalability of diagnostic-CT-enabled planning, compared to conventional CT simulation planning, for patients receiving PRT to bone, soft tissue and lung disease.

*Research Hypothesis: Diagnostic-CT-enabled planning for PRT patients is an effective, acceptable and scalable alternative to CT-simulation.*

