### Sample size calculation

Based on a review of recent same-day treatments at the London Regional Cancer Program (LRCP), the estimated TIC in the standard arm of this trial will be 4.8 hours, with a standard deviation of 2. We hypothesize that in the experimental arm, the estimated TIC will be 2.5 hours, with the same standard deviation. Using a two-sided, two-sample t-test, with a 1:2 randomization, alpha of 0.05 and power of 80%, adjusting for 10% dropout, 33 patients are required, 11 in the standard arm and 22 in the experimental arm.

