### Statistical analysis plan

Patients will be analyzed in the groups to which they are assigned (intention-to-treat). Comparisons between treatment arms for TIC (primary endpoint) will be performed using the two-sample t-test. TIC data is anticipated to be normally distributed. In the event such data is not normally distributed, non-parametric testing using the Wilcoxon rank sum test will be substituted as appropriate. For the secondary endpoints for efficacy (rate of plan deliverability and rate of plan acceptability on blinded review of dose distributions) and acceptability (stakeholder evaluations based on Likert scale), differences between treatment arms will be compared using the Chi-square test or Fisher’s exact test as appropriate. For the secondary endpoint for scalability based on the ISAT, differences between treatment arms will be compared using the two-sample t-test or substituted with Wilcoxon rank sum test if such data is not normally distributed, similar to primary endpoint.

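### Plan deliverability and plan acceptability carry the efficacy claim, but the only final analysis named for them is a between-arm test of difference at 11 v 22, which cannot show that Arm 2 is adequate

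*Protocol article*

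**What the plan says.** The research hypothesis (Protocol article, Objectives) is that diagnostic-CT planning "is an effective, acceptable and scalable alternative to CT-simulation".

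The Background explains that pain and treatment response were not chosen as endpoints, and that efficacy in this setting "is dependent upon the rate of plan deliverability" and on plan acceptability. Both are explained there by what the experimental arm produces: a plan that can be delivered, and a plan that meets institutional guidelines.

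The Statistical analysis plan section gives one method for these two rates: "differences between treatment arms will be compared using the Chi-square test or Fisher’s exact test as appropriate".

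The sample size section sizes the trial on time in centre (TIC) alone: "Using a two-sided, two-sample t-test, with a 1:2 randomization", "alpha of 0.05 and power of 80%, adjusting for 10% dropout", giving the result that "33 patients are required, 11 in the standard arm and 22 in the experimental arm".

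The only numerical floor for either rate is in the section on interim analysis. There, Arm 2 deliverability below 60% lets the team recommend, at its discretion, stopping the trial or dropping certain treatment sites.

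**The concern.** The hypothesis needs evidence that Arm 2 is good enough. The named method asks whether the arms differ. A significant result could count against Arm 2, but a non-significant one does not count for it, least of all in a small sample.

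The primary endpoint does not fill the gap, because TIC says nothing about plan quality. With pain and treatment response set aside, these two rates carry the efficacy claim. If the report relied on the p-value, a materially lower acceptability rate in Arm 2 could appear only as a non-significant difference. A score of 3 on the blinded review marks a deficiency that may affect clinical outcome, so such a shortfall would matter.

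**Working it through.** **1. The plan's own sample size (Sample size calculation section).** Inputs: means 4.8 and 2.5 hours, SD 2, two-sided alpha 0.05, power 80%, ratio 1:2. The standardised difference is (4.8 − 2.5)/2 = 1.15. The two-sample t-test then needs 9.59, so 10, in Arm 1 and 20 in Arm 2, 30 in all. Adding 10% gives 30 × 1.1 = 33, or 11 + 22. The stated figure is reproduced, and it concerns TIC only.

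**2. Where Fisher's test becomes significant.** Assumptions: plan acceptability is dichotomised (score 3 against 1 or 2), Arm 1 is 11/11, all 33 patients are evaluable, and the test is two-sided at 0.05. With f failures in total, the probability that k of them fall in Arm 1 is C(11,k) × C(22,f−k) / C(33,f). The two-sided p-value adds all tables no more probable than the one observed.

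- Arm 2 at 15/22 (68%), f = 7: the observed table (k = 0) has probability 0.0399. The tables at k = 5, 6 and 7 add 0.0250 + 0.0024 + 0.0001. p = 0.067, not significant.
- Arm 2 at 14/22 (64%), f = 8: the observed table has probability 0.0230. The tables at k = 6, 7 and 8 add 0.0077 + 0.0005 + 0.00001. p = 0.031, significant.

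So 15/22 is the lowest Arm 2 count that stays non-significant under these conditions.

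**3. How far the boundary moves.**

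| Condition | Lowest non-significant Arm 2 result | p |
|---|---|---|
| Arm 1 11/11, Fisher | 15/22 (68%) | 0.067 |
| Arm 1 10/11, Fisher | 12/22 (55%) | 0.054 |
| 10 v 20 evaluable, Arm 1 10/10, Fisher | 13/20 (65%) | 0.064 |
| Arm 1 11/11, uncorrected chi-square | 16/22 (73%) | 0.056 |
| Arm 1 11/11, continuity-corrected chi-square | 14/22 (64%) | 0.062 |

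The smallest expected counts near the boundary are below 5 (7 × 11/33 = 2.3 at 15/22), so Fisher's test is the one that would apply.

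**4. Power.** If the true Arm 1 rate is 100%, Arm 1 is always 11/11. Power is then the probability that Arm 2 has 14 or fewer acceptable plans: P(Bin(22, p) ≤ 14).

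| True Arm 2 rate | Power |
|---|---|
| 90% | 0.1% |
| 80% | 5.6% |
| 70% | 33% |
| 68% | 41% |
| 60% | 71% |

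With a true Arm 1 rate of 95% and Arm 2 at 75%, full enumeration gives 9.5%.

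**5. What the Arm 2 rate alone can show.** The exact (Clopper-Pearson) 95% lower limit for x of 22 is the 2.5% quantile of Beta(x, 23 − x). For 22/22 it reduces to 0.025^(1/22) = 0.846.

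| Arm 2 result | Exact 95% lower limit |
|---|---|
| 22/22 | 85% |
| 20/22 | 71% |
| 18/22 | 60% |
| 15/22 | 45% |

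**6. The between-arm difference as an estimate.** For 11/11 v 20/22, the Newcombe 95% interval for Arm 2 minus Arm 1 runs from −27.8 to +17.6 points. That interval conveys the uncertainty that a bare non-significant p-value hides.

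**The case against.** A reader might infer that the plan will pass Arm 2 at any acceptability rate down to 68%. The documents do not support that. The analysis section says only that the arms will be compared. It gives no decision rule and nowhere treats non-significance as success. The 68% is also conditional: it needs Arm 1 at exactly 11/11, no dropout, and a two-sided 0.05 level that the protocol states only for sizing TIC. Nor is a non-significant result close to certain at that rate, since power is 41% when the true Arm 2 rate is 68%. Near-certainty applies only to smaller deficits, at true Arm 2 rates of about 80% or more.

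It can also be said that the endpoints are listed as rates, that the Background frames them by what Arm 2 produces, and that the blinded review has explicit dose criteria. A poor Arm 2 rate would therefore be visible once reported. The 60% interim trigger shows that the team does not judge deliverability by a between-arm p-value alone. These are secondary endpoints of a 33-patient feasibility trial whose Limitations section admits restricted internal validity, and interval methods and thresholds are often left to a separate analysis plan.

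Much of this stands, and it limits the point. It does not remove it. The article does choose a final method for these two rates, and that method does not answer the hypothesis. The interim trigger is discretionary and covers deliverability only. Framing the endpoints as Arm 2 rates argues for analysing them as such.

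**Conclusion.** The point holds as a mismatch between hypothesis and method. The two rates that carry the efficacy claim have one named final analysis, a test of difference, in a sample sized for another endpoint. That test cannot establish adequacy, and its non-significance would be weak evidence: power is 5.6% against a true 20-point deficit from 100% and 33% against a 30-point deficit.

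The figures assume two-sided 0.05 and all 33 patients evaluable; the boundary of 15/22 also assumes 11/11 observed in Arm 1. One Arm 1 failure or the planned dropout lowers the boundary, and an uncorrected chi-square test would raise it to 16/22. How the team would interpret a non-significant result is not stated, so no wrong conclusion can be attributed to the plan. The change is worth making because it is cheap and matches the protocol's own account of efficacy.

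**What to change.** In the Statistical analysis plan section:

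- Make the Arm 2 rate with its exact 95% confidence interval the main analysis of primary plan deliverability and of plan acceptability.
- State the denominator for each. The blinded review scores the delivered plan, which in Arm 2 may be a CBCT back-up plan or may not exist if treatment is deferred, so 22 scored diagnostic-CT plans are not assured. Show CBCT back-up plans separately.
- Read each interval against a minimum rate that the team sets before the outcome data are analysed. The trial is open-label, so the timing should be tied to the analysis and not to an unblinding. The rate itself is the team's choice.
- Give the between-arm difference with its confidence interval descriptively, and state that a non-significant difference is not evidence of an acceptable alternative.

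The cost is wording only, with no added patients, data or procedures. A powered non-inferiority comparison is not a realistic substitute. With an assumed true rate of 95% in both arms, one-sided 0.025, 80% power and 1:2 allocation, it would need 42 patients before dropout even for a 20-point margin, and 168 for a 10-point margin. The downside is a less favourable conclusion: 20/22 would exclude only rates below 71%.

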### Endpoints

#### Primary endpoints

The primary endpoint is time in centre (TIC) on the treatment day. This is defined as the total time in hours spent at the cancer centre from the scheduled CT simulation (Arm 1) or treatment delivery (Arm 2) appointment until beam delivery completion.

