##### Undeliverable plan

Plans may be deemed undeliverable in the following scenarios:The treatment position could not be reproduced within tolerance *and* there is significant anatomical or external contour variation that cannot be corrected with IGRTProgression has occurred such that the target volume requires expansion for adequate coverageChanges are observed on CBCT that contraindicate PRTCBCT reveals new findings such as interval development of pathological fracture, atelectasis, etc. which warrant PRT deferral for further assessment or involvement of other services

At the discretion of the RO, CBCT-enabled planning may be enacted if a diagnostic-CT-enabled plan is considered undeliverable. This process is described in the next section.

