## Data collection and evaluation of efficacy, acceptability, and scalability

### Efficacy

#### Primary endpoint: time in centre (TIC)

TIC is defined as the total time in hours spent at the cancer centre and will be measured as follows:*Arm 1*: Scheduled CT simulation appointment time to time of beam delivery completion.*Arm 2*: Scheduled radiation treatment appointment time of beam delivery completion.

If machine/technical/patient-related delays or other unforeseen circumstances cause a delay to appointment time of more than 15 minutes, start time will be recorded and an adjusted TIC will be calculated based on the actual appointment start time. The intention of the adjusted TIC is accurate capture of TIC under normal operating conditions.

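### Time in centre has no value, or only a later day's value, for a patient not treated on the treatment day, so the primary comparison is not fully intention-to-treat

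*Protocol article*

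**What the plan says.** All references are to the protocol article.

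- **Endpoints, Primary endpoints.** "The primary endpoint is time in centre (TIC) on the treatment day". The clock starts at the scheduled CT simulation in Arm 1 "or treatment delivery (Arm 2) appointment until beam delivery completion".
- **Primary endpoint: time in centre (TIC).** The Arm 1 rule is "Scheduled CT simulation appointment time to time of beam delivery completion"; Arm 2 starts from the scheduled radiation treatment appointment and has the same stop point. For delays of more than 15 minutes, "an adjusted TIC will be calculated based on the actual appointment start time". That moves the start of the clock and leaves its end alone.
- **Undeliverable plan (under Arm 2).** Four scenarios are listed. One is a CBCT change that contraindicates palliative radiotherapy; another is new findings "which warrant PRT deferral for further assessment or involvement of other services". The back-up is optional: "At the discretion of the RO, CBCT-enabled planning may be enacted if a diagnostic-CT-enabled plan is considered undeliverable".
- **Statistical analysis plan.** "Patients will be analyzed in the groups to which they are assigned (intention-to-treat"). The arms are compared on TIC by a two-sample t-test, or by the Wilcoxon rank sum test if the data are not normal.

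**The concern.** A clock that stops only at beam completion has no reading when no beam is delivered. The protocol itself expects some Arm 2 visits to end that way. The patient then has no primary-endpoint value. If the patient comes back, the Arm 2 clock starts at the new treatment appointment, so neither the failed visit nor a simulation done in between is counted.

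Whether a value is lost depends on how the assigned workflow turned out, so the loss is related to the outcome. Assigning patients to their randomised arm does not cure this, because a patient without a TIC cannot enter a t-test. The primary result could then show the planned time saving while leaving out the visits where the new workflow cost the patient extra time.

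**Working it through.** **1. The plan's own figure.** Inputs from Sample size calculation: means 4.8 and 2.5 h (difference 2.3 h), SD 2, two-sided alpha 0.05, 80% power, ratio 1:2, 10% dropout. Noncentral-t power is 77.3% at 9 v 18 and 81.8% at 10 v 20, so 30 evaluable patients are needed. 30 × 1.1 = 33, which matches the stated 11 and 22. The sample size is not in question.

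**2. Who has a TIC under the definition?**

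| Course of the visit | TIC as defined |
|---|---|
| Arm 2, diagnostic-CT plan delivered | Yes |
| Arm 2, plan undeliverable, CBCT plan delivered the same day | Yes, and probably long (re-contouring, new plan, QA, repeat CBCT) |
| Arm 2, no beam that day, treated later | Only the later treatment appointment |
| Arm 2, no beam ever | None |
| Arm 1, simulated but not treated that day | No same-day value |

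Only the last three rows are affected. The undeliverable-plan section belongs to Arm 2. Patient inclusion criteria allow a diagnostic scan up to 28 days old at enrolment, whereas Arm 1 plans on a same-day simulation. The loss is therefore likely, though not certain, to fall mainly on Arm 2.

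**3. Effect on the estimate (illustration).** Let f be the share of Arm 2 not treated that day and v the length of the failed visit. The documents give neither. Assume that v = 1.5 h, that each such patient then has a conventional 4.8 h day, and that Arm 2 patients treated the same day average 2.5 h.

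As written, with the untreated dropping out (or entering with a later treatment-appointment value averaging 2.5 h): 4.8 − 2.5 = 2.3 h for any f.

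Counting all time: saving = 4.8 − [(1 − f) × 2.5 + f × (v + 4.8)]. With v = 1.5 this is 2.3 − 3.8f.

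| f | Saving counting all time | Overstatement |
|---|---|---|
| 5% | 2.3 − 0.19 = 2.11 h | 0.19 h |
| 10% | 2.3 − 0.38 = 1.92 h | 0.38 h |
| 20% | 2.3 − 0.76 = 1.54 h | 0.76 h |

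At f = 20%, v = 1.0 h gives 2.3 − 0.2 × 3.3 = 1.64 h, and v = 2.5 h gives 2.3 − 0.2 × 4.8 = 1.34 h. Of 22 Arm 2 patients, two to four untreated would be 9% to 18%.

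**4. Effect on power.** Noncentral t, removing Arm 2 patients from the randomised 11 v 22 with no other dropout: 85.5% at 11 v 22, 84.2% at 11 v 20, 82.6% at 11 v 18 and 80.6% at 11 v 16. The loss is minor.

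**5. Would stopping the clock at departure work?** With a 1.5 h abandoned visit in 20% of Arm 2, the Arm 2 mean is 0.8 × 2.5 + 0.2 × 1.5 = 2.3 h, and the apparent saving rises to 4.8 − 2.3 = 2.5 h. The rule would reward failure.

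**6. How much can the handling rule matter?** In 4,000 simulated trials per setting (11 v 22, normal TIC), ranking every untreated Arm 2 patient worst in a Wilcoxon test cut the chance of a significant result from about 83% with none untreated to about 50% at 10% and 20% at 20%. The complete-case t-test stayed at about 83% and 82%. Worst rank for all is an extreme choice, but it shows that the conclusion can turn on a rule the protocol does not state.

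**The case against.** The strongest reply is that handling of missing primary values is commonly left to the SAP, which is not shown, and that the protocol never says untreated patients are excluded. Both statements are true. But the gap lies in the endpoint definition that the protocol fixes: under it, time spent at a failed visit is not part of TIC.

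Several stronger readings are tempting, and the documents do not support them:

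- *A reader might infer that Arm 2 is analysed only where the diagnostic-CT plan worked.* Patients rescued by same-day CBCT planning keep a TIC and count in Arm 2.
- *A reader might infer from the 60% threshold under Interim analysis/early trial discontinuation that up to 40% of Arm 2 could go untreated, against a 10% dropout allowance.* The threshold concerns plan deliverability. Plan deliverability is split into primary (diagnostic-CT plan) and secondary (CBCT plan), so an undeliverable first plan is not a patient leaving untreated.
- *A reader might infer that Arm 1 is complete.* It has the same stop point and also requires a CBCT at fraction 1, and Background notes that conventional waits dissuade some patients from same-day service. Losing long Arm 1 days would count against Arm 2.
- *A reader might infer that failures are hidden.* Undeliverable plans are a secondary endpoint, with documented reasons and an alert within 24 hours. That keeps them visible but does not correct the primary estimate.

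It also stands that contraindication or deferral can reflect disease change rather than workflow failure, that no return for simulation is described, and that the one earlier cohort cited (30 patients) had 100% deliverability. That last point is only partly reassuring, since this trial adds thoracic targets.

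**Conclusion.** The point holds in a limited form. The definition leaves patients not treated on the treatment day with no TIC, or with a later value that omits the failed visit and any simulation, and the intention-to-treat statement cannot repair that. The likely direction favours Arm 2, but this is plausible rather than established. Under the assumptions shown, the saving is overstated by 0.19 h at 5% untreated, 0.38 h at 10% and 0.76 h at 20%. The true rate is unknown, and with no untreated patients there is no bias. Power is not the issue: from 11 v 22 it stays above 80% down to 11 v 16.

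**What to change.** Make the change before outcome data are seen. It concerns measurement only, not how patients are managed.

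1. In both arms, define TIC as total time in centre summed over all visits, from the first scheduled simulation or treatment appointment until fraction 1 is completed. Include any visit that ended without beam delivery and any later simulation.
2. For patients who never receive fraction 1, do not stop the clock at departure. Pre-specify an unfavourable value, such as worst rank in a Wilcoxon sensitivity analysis, and report their number by arm.
3. Keep the comparison restricted to patients treated on the same day as a sensitivity analysis.

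The cost is protocol wording and departure times for a few patients. The endpoint would no longer be confined to a single treatment day, so its description must change to match. If plans fail, the Arm 2 saving will look less favourable, and worst-rank scoring will lower the chance of a significant result.
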